### Statistical Analysis

After the research trial is finalized, a statistical professional is responsible for developing a statistical analysis plan in consultation with the principle investigator. The statistical analysis software (SAS® 9.2 software) will be used.

#### Analysis Subjects

The research subjects will be divided into the following categories:

1. Full Analysis Set (FAS)□ FAS refers to the data set obtained from all randomized subjects with the least amount and reasonable method of eliminating subjects. Exclusions usually include violations of important inclusion criteria; subjects do not receive treatment with the test medication; no observational data is obtained after randomization.2. Per Protocol Set (PPS)□ PPS is a subset of the full analysis set, and these subjects are more compliant with the trial. Subjects included in the PPS generally have the following characteristics: (1) the minimum exposure of the research drug in advance-completion, that is, the compliance with the drug is 80%; (2) the data of the primary outcomes in the test are available; (3) no major violation of the protocol.3. Security data set (Safety Set, SS)□ SS is a subject who received at least one-time treatment after randomization and has a safety assessment.

#### Statistical Analysis Method

□ All statistical tests will be performed using a two-sided test, and a *p* <0.05 (two-sided test) will be considered to be statistically significant results (except for special instructions).□ Descriptive analysis: This data is described by the number of cases and the composition ratio. The measurement data are described by means of mean, standard deviation, maximum value, and minimum value. The non-normal distribution data are described by median, 25th and 75th quantiles. A comparison between the two groups of general conditions will be based on outcomes. Quantitative data will be compared between groups using group *t*-test or Wilcoxon rank sum test, classification data using chi-square test, or exact probability method, grade data used Wilcoxon rank sum test, or CMH test, as appropriate.

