### Eligibility Criteria

#### Inclusion Criteria

Subjects are between 18 and 70 years of age;After the run-in period, subjects should meet the diagnostic criteria for metabolic syndrome (3, 6):

Indispensable indicators:Abdominal obesity (central obesity): waist circumference in male ≥ 90 cm, female ≥ 85 cm;Other indicators:At least two of the following four indicators can diagnose metabolic syndrome:① Hyperglycemia: fasting blood glucose (FBG) ≥ 6.1 or 2 h after glucose load (2HPG) ≥ 7.8 mmol/L and/or have been diagnosed as diabetes and received treatments.② Hypertension: blood pressure ≥ 130/85 mmHg and/or have been confirmed to be hypertension and received related treatments.③ Fasting TG ≥ 1.70 mmol/L.④ Fasting HDL-C <1.04 mmol/L.

3. After the run-in period, subjects should meet the diagnostic criteria for impaired glucose tolerance:(a) Impaired fasting glucose (IGT): FBG < 7.0 mmol/L and 2HPG: 7.8–11.1 mmol/L.

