### Outcome Measure

#### Primary Outcomes

Incidence of type 2 diabetes.

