### Sample Size Calculation

According to “Lian et al. (23),” after 1 year of follow-up, the average annual incidence of diabetes in the placebo group was 29.32%. “Gao et al. (24)” demonstrated a cumulative incidence of diabetes in placebo group after 3 years of follow-up was 43.86%.

Our hypothesis assumes that the incidence of diabetes in the control group would be 40.0% after 2 years of intervention and the HR would be expected to be 0.75—the study drug is predicted to reduce the risk by 25%—employing α = 0.05, β = 0.20. The study group and the control group will be allocated in a 1:1 ratio. The study period will last 4 years, including 2 years of medication treatment and 2 years of follow-up. PASS16 software will be employed to calculate the sample size, each group should contain 395 subjects. Considering a 10% the violation rate and issues of inter-center case allocation, a total of 880 cases and evaluation of number of endpoint events 209:171 will be required to reach statistical significance.

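### Naming baseline glucose and HbA1c as covariates would add power to the diabetes comparison at almost no cost; the unadjusted tests listed are valid but leave this unused

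*Protocol article*

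**What the plan says.** - **Primary outcome.** The Primary Outcomes section reads "Incidence of type 2 diabetes" and attaches no test or model.
- **Tests.** The Statistical Analysis Method section says "Quantitative data will be compared between groups using group *t*-test or Wilcoxon rank sum test, classification data using chi-square test, or exact probability method". It then lists Wilcoxon or CMH for graded data. CMH can be stratified, but no stratification factor is named. No regression model or covariate appears anywhere in the article.
- **Sample size.** The Sample Size Calculation section assumes that "the incidence of diabetes in the control group would be 40.0% after 2 years of intervention" and that "the HR would be expected to be 0.75", "employing α = 0.05, β = 0.20", with 1:1 allocation. It mentions no covariate.
- **Baseline data.** Table 1 marks the OGTT and glycated hemoglobin at the random enrollment visit (days −7 to 0). Entry after the run-in requires "FBG < 7.0 mmol/L and 2HPG: 7.8–11.1 mmol/L", so both glucose values must be known for every eligible subject.
- **Analysis plan.** The Statistical Analysis section leaves a detailed plan to be developed later.

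**The concern.** Diabetes is followed in this trial through capillary glucose and OGTT, and subjects enter with 2-hour glucose anywhere between 7.8 and 11.1 mmol/L. They therefore start at different distances from the upper limit of the entry range. Fasting glucose has no lower entry limit and HbA1c has none at all. Such baseline values are natural candidates for predicting who develops diabetes.

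In a time-to-event comparison, leaving out a strong predictor pulls the hazard ratio toward 1 and costs power. That applies to an unadjusted log-rank test or Cox model as much as to a chi-square test, so the point is separate from the choice between those methods. The trial is sized at 80% power with no reserve beyond the 10% allowance for protocol violations. What is at stake is a gain in power from data already being collected.

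**Working it through.** **1. Reproduce the plan's figures without covariates.** The inputs from the Sample Size Calculation section are 40% control incidence at 2 years, HR 0.75, α 0.05, β 0.20, 1:1 allocation and 4 years in total. The Statistical Analysis Method section makes tests two-sided, and the Study Objectives section gives 2 years of accrual (taken as uniform).

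- Events (Schoenfeld): 4 × (1.960 + 0.842)² / (ln 0.75)² gives 380 after rounding up.
- Control hazard: −ln(0.60)/2 = 0.2554 per year. Treated hazard: 0.75 × 0.2554 = 0.1916.
- Event probability with 2-year accrual and close at year 4: 1 − (e^(−2λ) − e^(−4λ))/(2λ).
  - Control: 1 − (0.600 − 0.360)/0.5108 = 0.530.
  - Treated: 1 − (0.6817 − 0.4648)/0.3831 = 0.434.
- Per arm: 380/(0.5302 + 0.4337) = 394.3, so 395. Events: 394.3 × 0.5302 = 209 and 394.3 × 0.4337 = 171.
- Allowance: 395/0.90 = 439 per arm, or 878, stated as 880.

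All the stated figures follow. The 80% power therefore already assumes no adjustment.

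**2. Add a baseline score.** The documents give no prognostic strength, so this step rests on an assumption. Two separate simulations used 395 per arm, the same accrual and follow-up, control incidence of 40% at 2 years, and one standard-normal baseline score with log hazard ratio b per SD. The treatment effect was set so that the unadjusted HR stayed near 0.75 (0.74 to 0.75 in the second).

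| b per SD (HR per SD) | First: unadjusted → adjusted (4000 trials) | Gain | Second: unadjusted → adjusted (1500 trials) | Gain |
|---|---|---|---|---|
| 0.3 (1.35) | 79.7% → 82.2% | 2.5 | 80.6% → 82.1% | 1.5 |
| 0.5 (1.65) | 79.9% → 85.0% | 5.1 | 80.8% → 85.7% | 4.9 |
| 0.7 (2.0) | 79.6% → 88.2% | 8.6 | 83.1% → 89.5% | 6.4 |

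Monte Carlo error in the second run is about 1 point on each power. Its gain at 0.7 is smaller partly because it started from 83%. A further simulation gave 1–2, 5–6 and 8 points at the three strengths, and similar gains when the score was limited in range (uniform) rather than normal.

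**3. Same direction with a comparison of proportions.** On whole-study proportions of 53.0% and 43.4%, a chi-square test at 395 per arm has 77.6% power. Adjustment that explains a share R² of outcome variance acts like 395/(1 − R²) per arm:

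- R² = 0.02: power 78%.
- R² = 0.10 (395/0.90 = 439): power 82%.
- R² = 0.20 (395/0.80 = 494): power 86%.

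**4. Size of the downside.** In the second simulation the adjusted HR was 0.741, 0.728 and 0.708 at b = 0.3, 0.5 and 0.7, against unadjusted 0.747, 0.745 and 0.740.

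**The case against.** The strongest objection is that a covariate set is ordinary content for an analysis plan, which the article says is still to come, so its absence is no defect. That stands: nothing is faulted here for being missing, and the point is a recommendation about the method stated.

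Stronger readings are tempting, and the documents do not support them:

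- **That the primary comparison is fixed as unadjusted.** The test list sits under a descriptive-analysis bullet, right after a comparison of general conditions, and is not tied to diabetes incidence. It suggests an unadjusted primary test but does not fix one.
- **That the trial is underpowered for lack of covariates.** Step 1 shows that the sample size was built for an unadjusted log-rank analysis and meets 80% on those terms.
- **That unadjusted power is only about 68% to 74%.** Those values arise at b = 0.7 and 0.5 if 0.75 is read as an HR conditional on baseline glycaemia. The Sample Size Calculation section mentions no covariate, and its event counts reproduce from the marginal reading.
- **That chance imbalance in baseline glucose would invalidate the result.** The Randomization section names no stratification factor, but it does not say that allocation is unstratified. In either case the unadjusted test keeps its type I error. Adjustment improves precision; it does not repair a bias.

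It is also fair to object that the entry limits narrow the glucose range and that the Discussion expects measurement error across centers. Both could weaken prediction. The range-limited simulation shows that restricted entry does not remove the benefit at a given strength, but the true strength may lie at the low end, where the gain is small.

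**Conclusion.** The point holds as an improvement and not as an error. The tests listed are unadjusted, the sample size is an unadjusted log-rank calculation, and suitable baseline covariates are already scheduled. An unadjusted log-rank or Cox analysis would be valid and would give the planned 80%.

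Adjustment would add about 1 to 2 points of power at an assumed log hazard ratio of 0.3 per SD, about 5 at 0.5, and up to about 8 to 9 at 0.7. These figures assume proportional hazards, a single well-measured score and a marginal HR near 0.75. The documents cannot say where in the range this trial lies.

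**What to change.** State the primary analysis of diabetes incidence as a Cox model with treatment and three continuous covariates from the random enrollment visit: 2-hour OGTT glucose, fasting glucose and HbA1c. Report the unadjusted analysis alongside, and say which hazard ratio is conditional and which is marginal.

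Fix this before unblinding. The article's timing for the analysis plan can be read as after the design is final or after the trial has finished, so the date should be made explicit.

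The cost is one sentence in the statistical section or the analysis plan. No new visits, tests or subjects are needed, and the sample size can stay as it is. The conditional hazard ratio lies somewhat further from 1 than the marginal one, which is why both should be shown.

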### Safety Assessment

The subjects will be described as the normal before treatment and the abnormal cases after treatment, rating the proportion of the number of cases. Adverse events will be described by the number of occurrences, the number of cases, and the incidence of adverse events. The incidence will be tested for significance between groups. At the same time, the specific performance and extent of all adverse events in each group of cases and their relationship with drugs should be described in detail.

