#### Exclusion Criteria

Subjects who have used hypoglycemic drugs in the past 3 months;Hyperthyroidism or hypothyroidism caused by endocrine disorders;Uncontrollable hypertension/hypotension: systolic blood pressure ≥200 mmHg or diastolic blood pressure ≥110 mmHg; or systolic blood pressure ≤ 90 mmHg, or diastolic blood pressure ≤ 60 mmHg;Comorbidities such as various acute infections, or severe infections, severe anemia, and neutropenia;Major disease comorbidities, such as active or untreated malignant tumors, or clinical remission of malignant tumors <5 years ago;Natural heart disease, such as congenital heart disease, rheumatic heart disease, hypertrophic or dilated cardiomyopathy, New York Heart Association (NYHA) cardiac function classification > III level;Subjects who had any of the following conditions within the past 6 months: coronary intervention (e.g., CABG or PTCA), stroke (including ischemic and hemorrhagic stroke);Severe liver and kidney dysfunction (ALT three times greater than the upper limit of the normal and creatinine >132 μmol/l);After the run-in period, fasting TG is <5.6mmol/L;Pregnant or lactating women, and women of childbearing age who have not taken effective contraceptive measures;Participation in any other clinical trials;For any reason, the investigator may consider a subject inappropriate for participation in this study.

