**Safety indicators**																
Blood/urine routine		•						•						•	※	•
Liver and kidney function		•						•						•	※	•
12-lead ECG		•						•						•	※	•
Serum NO, E-1		•												•	※	•
Thyroid function		•														
NYHA classification		•														
Adverse event assessment	•	•	•	•	•	•	•	•	•	•	•	•	•	•	•	•

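### The only before/after safety summary stated counts moves from normal to abnormal, so it omits worsening in subjects admitted with a raised ALT and ignores how large a change is

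*Protocol article*

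**What the plan says.** The Safety Assessment section of the protocol article opens with the before/after rule: "The subjects will be described as the normal before treatment and the abnormal cases after treatment", with the result expressed as a proportion. It does not name the measurements. Adverse events have their own sentences, and Table 1 lists repeated safety tests (blood and urine routine, liver and kidney function, 12-lead ECG), so the rule most naturally applies to those tests.

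The same section then turns to adverse events: "Adverse events will be described by the number of occurrences, the number of cases, and the incidence of adverse events". Incidence is to be tested between groups, and "the specific performance and extent of all adverse events in each group of cases and their relationship with drugs should be described in detail". No condition on baseline status is attached.

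The Exclusion Criteria set the organ-function limit as "Severe liver and kidney dysfunction (ALT three times greater than the upper limit of the normal and creatinine >132 μmol/l". In Table 1, "Liver and kidney function" is measured at randomization and months 6 and 12, then on the same pattern to month 48, and at an end event.

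The Statistical Analysis Method section adds a general descriptive rule, not confined to efficacy data: "The measurement data are described by means of mean, standard deviation, maximum value, and minimum value".

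**The concern.** The summary rule and the eligibility rule do not fit together. The summary starts from subjects who are normal before treatment, while eligibility lets in subjects who are not. The population has abdominal obesity and metabolic syndrome, so some raised ALT values at entry are to be expected, although the document gives no rate.

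The rule is also binary. It records that a limit was crossed, but not by how much.

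Safety is a stated aim and treatment lasts 24 to 48 months. The before/after table would be the natural place to look for a liver or kidney signal across the arms. As stated, it is poorly able to show a signal that arises in subjects with an abnormal baseline, or one that consists of a few large rises among many small crossings.

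**Working it through.** The plan gives no figure to reproduce. The check sets the two rules side by side and then sizes the gap under stated assumptions.

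**Step 1. Which changes are counted?** The ALT values below are hypothetical.

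| Baseline ALT | Worst later ALT | Eligible? | In the normal-to-abnormal count? |
|---|---|---|---|
| 0.99 × ULN | 1.01 × ULN | yes | yes, as one subject |
| normal | 10 × ULN | yes | yes, as one subject, same weight |
| 1.5 × ULN | 10 × ULN | yes | no |
| 2 × ULN | 10 × ULN | yes | no |

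The text does not state the denominator of the proportion. This does not matter here, because a subject abnormal at baseline cannot add to the numerator under either choice.

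**Step 2. Who can be abnormal at entry?** On the strict reading, either limit alone excludes, and ALT above 1 and up to 3 × ULN is still admitted. On the literal reading of the joining word, a subject is excluded only when both limits are exceeded, so ALT above 3 × ULN may enter if creatinine is not above 132 μmol/l. ALT is therefore a firm example on both readings. Creatinine is weaker. The document gives no ULN for it, so whether a value up to 132 μmol/l is raised is an assumption. Creatinine above 132 μmol/l enters only on the literal reading.

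**Step 3. How many subjects could be affected?** The sample size is 880 at 1:1, so 880 / 2 = 440 per arm. With an assumed abnormal-baseline share f for a given test:

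- f = 10%: 0.10 × 440 = 44 per arm
- f = 40%: 0.40 × 440 = 176 per arm

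These subjects cannot contribute to that test's count.

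**Step 4. What share of marked rises falls outside the count?** Let r be the risk of a marked rise in subjects with an abnormal baseline relative to those with a normal one. Then

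share outside = f·r / (f·r + 1 − f)

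| f (assumed) | r = 1 | r = 2 (assumed) |
|---|---|---|
| 10% | 0.1 / 1.0 = 10% | 0.2 / 1.1 = 18% |
| 20% | 0.2 / 1.0 = 20% | 0.4 / 1.2 = 33% |
| 30% | 0.3 / 1.0 = 30% | 0.6 / 1.3 = 46% |
| 40% | 0.4 / 1.0 = 40% | 0.8 / 1.4 = 57% |

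These shares refer to the before/after count alone. They give no credit for rises that surface by another route.

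**Step 5. Do the other routes supply the missing count?**

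- *Adverse events.* A laboratory worsening appears here only if it is reported as an event, and the article gives no laboratory threshold for doing so.
- *Mean, standard deviation, maximum, minimum.* These are group-level. A few large rises hardly move a mean, and a maximum shows one subject.
- *Withdrawal for abnormal results.* This requires a clear relation to the study drug, and it governs conduct rather than analysis.

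None of the three gives the number of subjects per arm who worsened from an abnormal baseline.

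**The case against.** The strongest reply is that the before/after line is one condensed sentence in a journal article. It names neither laboratory tests nor ECG and does not say that nothing else will be tabulated. The article says a statistical analysis plan will follow, and shift tables and grading limits usually belong there. Adverse events are assessed at every visit, counted without regard to baseline and tested between groups. An ALT rising from 1.5 to 10 × ULN is the kind of result that reporting should pick up, and it would also show in the maximum.

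Much of this stands. A reader might infer that worsening from an abnormal baseline is never counted. The documents do not support that, because the adverse-event counts and the measurement summaries both remain open to it. A reader might also infer that a formal liver and kidney comparison leaves these subjects out. That is not supported either. The before/after line is descriptive, and the significance test, read in order, belongs to adverse-event incidence. Applying the line to laboratory tests is an inference from Table 1.

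The appeal to a later plan does not remove the point. The matter is not an absent detail but a summary that the article does state, and a plan that follows the article would inherit its gap.

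**Conclusion.** The point holds in a limited form. The one before/after safety summary stated cannot register worsening from an abnormal baseline, eligibility admits such baselines at least for ALT, and the count does not separate small changes from large ones. The remaining routes depend on investigator reporting or on group-level statistics.

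The size is unknown from the document. The 10–40% range rests on an assumed share of abnormal baselines and equal risk of a marked rise; the larger values in the table also need an assumed doubling of risk. The gap exists at any share above zero.

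Severity is low to moderate. Neither the primary outcome nor the sample size is touched. The documents do not support saying that a safety signal would go undetected, only that this table would be a weak place to find one.

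**What to change.** Replace or supplement the normal-to-abnormal count with a shift table by arm for all Safety Set subjects, setting baseline category against worst post-baseline category for each repeated safety test. Use a standard grading fixed before unblinding. Bands such as ALT ≤1, >1–3, >3–5 and >5 × ULN, or creatinine as fold change from the subject's own baseline, are illustrations only. Report the number and proportion per arm in the marked categories, and keep the normal-to-abnormal count as a descriptive line with its denominator stated. If the full analysis plan already has such a table, the Safety Assessment wording need only be aligned with it.

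The cost is a sentence or two of text and a few more tables. No new visits or measurements are needed, because Table 1 already schedules the values at randomization, at the 6-monthly visits and at an end event.

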### Study Procedure

Figure 1 shows the study flow and Table 1 shows the study time schedule. The study will include run-in period, random enrollment, and treatment period. The run-in period was 1 month, and treatment period is at least 2 years. All the subjects will receive oral and written information regarding the study. Written informed consent will be obtained by the doctors involved in the trial.

**Table 1 T1:** Study flow chart.

**Research phase**	**Run-in**	**Random enrollment**	**Treatment period**													
Time	−1 Month	−7–0 days	1 M ± 7days	2 M ± 7	3 M ± 7	4 M ± 7	5M ± 7	6 M ± 7	7 M ± 7	8 M ± 7	9 M ± 7	10 M ± 7	11 M ± 7	12 M ± 7	Until the 48th month^#^	When an end event occurs

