### Intervention Cycles

Eligible subjects will be randomly assigned to receive general lifestyle intervention + Jinlida granules at a dose of 9 g or general lifestyle intervention + placebo, orally, three times daily. The run-in period is 1 month, and the intervention will last 24–48 months. Follow-up will last 24 months.

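### Adverse-event incidence is tested between arms with no allowance for exposure; if observation stops at diabetes, as Table 1 implies, the test is tilted against Jinlida, modestly for most individual events

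*Protocol article*

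**What the plan says.** The Safety Assessment section sets the summary measures: "Adverse events will be described by the number of occurrences, the number of cases, and the incidence of adverse events". It then commits to a comparison: "The incidence will be tested for significance between groups". The denominator of that incidence is not defined.

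The Statistical Analysis Method section assigns the tests by data type, with "classification data using chi-square test, or exact probability method", and all tests "will be performed using a two-sided test, and a *p* <0.05 (two-sided test) will be considered to be statistically significant results". The safety set has no minimum exposure: "SS is a subject who received at least one-time treatment after randomization and has a safety assessment".

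On how long patients are observed, the article gives several statements:

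- Table 1 ends with a separate column, "When an end event occurs". Drug recovery, closing laboratory tests, ECG and an adverse-event assessment are marked there. Dispensing is not marked, and no visit follows.
- Intervention Cycles: "the intervention will last 24–48 months", and a follow-up of 24 months is also mentioned.
- Treatment: a minimum of two years, with no exception for patients who develop diabetes.
- Sample Size Calculation: a four-year study made up of two years on medication and two of follow-up.
- Withdrawal Criteria: diabetes is not listed.

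**The concern.** The primary outcome is incident type 2 diabetes, and the trial hypothesis is that it comes later on Jinlida. If a patient's drug and adverse-event observation close at diabetes, time at risk depends on the very outcome that the drug is meant to change. The Jinlida arm would then collect more person-time, and a comparison of the proportion of patients with an event would show more events there even if the drug caused none. The distortion would grow with efficacy and with the frequency of the event. It would therefore be largest in a successful trial and for the overall comparison of any adverse event.

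**Working it through.** **Inputs from the article.** Control incidence 40.0% at 2 years, hazard ratio 0.75, "employing α = 0.05, β = 0.20", 1:1 allocation, 395 per arm before a 10% allowance, 880 in total (440 per arm), 2-year enrolment within a 4-year study.

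**Assumed.** Constant hazards; no other dropout; a first-adverse-event rate m that is equal in both arms (no true harm) and unaffected by diabetes; observation ending at diabetes or at the study's end. The article gives no adverse-event rate, so a range is shown.

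**Step 1: reproduce the plan's figures.**

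- Hazards: λ(control) = −ln(0.60)/2 = 0.2554 per year; λ(Jinlida) = 0.75 × 0.2554 = 0.1916.
- With follow-up uniform over 2-4 years, P(diabetes) = 1 − (e^(−2λ) − e^(−4λ))/(2λ).
- Control: 1 − (0.600 − 0.360)/0.5108 = 0.530. Jinlida: 1 − (0.6817 − 0.4648)/0.3831 = 0.434.
- Events at 395 per arm: 209 and 171, as stated. The Schoenfeld formula gives 4(1.960 + 0.842)²/(ln 0.75)², or 380 events, which equals 209 + 171. Then 790/0.9 = 878, against 880 stated.

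The 2-4 year follow-up model is therefore the one behind the plan's own numbers.

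**Step 2: exposure if observation stops at diabetes.** Mean time at risk = P(diabetes)/λ.

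- Control: 0.530/0.2554 = 2.08 years (× 440 = 913 person-years).
- Jinlida: 0.434/0.1916 = 2.26 years (× 440 = 996 person-years). The ratio is 1.09.
- Medication capped at 2 years, (1 − e^(−2λ))/λ: 1.57 and 1.66 years. The ratio is 1.06.

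**Step 3: the crude test with equal true rates.** The proportion with an event is the average over t in 2-4 years of m/(m+λ) × (1 − e^(−(m+λ)t)). For m = 0.2:

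- Control: 0.4392 × 0.736 = 32.3%. Jinlida: 0.5107 × 0.683 = 34.9%.
- The pooled proportion is 0.336, so SE = √(2 × 0.336 × 0.664/440) = 0.0318. The expected z is 0.0257/0.0318 = 0.81.
- Two-sided rejection is 12.7%, of which 12.4% is against Jinlida (nominal 5% and 2.5%).

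| m per year | Control | Jinlida | Rejects (total) | Against Jinlida |
|---|---|---|---|---|
| 0.01 | 2.0% | 2.2% | 5.4% | 3.8% |
| 0.02 | 4.0% | 4.4% | 5.8% | 4.5% |
| 0.05 | 9.7% | 10.6% | 7.0% | 6.2% |
| 0.1 | 18.2% | 19.8% | 9.0% | 8.5% |
| 0.2 | 32.3% | 34.9% | 12.7% | 12.4% |
| 0.5 | 58.6% | 62.5% | 21.3% | 21.2% |
| 1.0 | 77% | 81% | 27.0% | 26.9% |

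With the 2-year cap, total rejection runs from 5.7% (7.5% vs 7.9% with an event) to 17.5% (73% vs 76%). At a hazard ratio of 0.5 over 2-4 years, events in 18.2% vs 21.5% give 23%.

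**Step 4: does person-time cure it?** In 4,000 simulated trials per setting, a rate test (first events over time to first event, diabetes or study end) rejected 4.9%, 4.7% and 5.4% of the time at m = 0.1, 0.2 and 0.5. The crude test on the same data rejected 8.8%, 12.9% and 22.0%.

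**The case against.** A reader might infer that the plan ends drug and observation at diabetes and that its safety test will therefore produce false signals. The article supports neither statement at that strength.

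- **Stopping at diabetes is an inference.** It rests on the layout of one Table 1 column. Drug recovery is also marked at ordinary three-monthly visits, so the missing dispensing mark and the absence of a later visit carry the argument. The Withdrawal Criteria and Treatment sections say nothing to that effect, and the follow-up mentioned elsewhere could mean that adverse events are collected to a common end. This stands, and it makes the point conditional.
- **The crude proportion is an inference too.** Incidence is undefined, the article also uses the word for an annual rate, and the analysis plan could define it by person-time. This stands in part. The article does commit to a significance test, and the only tests it names for such data are tests of proportions, so that is the natural reading and not mere silence.
- **Small effect for individual events.** This stands: rejection is close to nominal for rare events, and the large figures need very common events. Events clustered soon after the start of treatment, before most diabetes endpoints, would shrink the bias further.
- **A different question.** The proportion of patients with an event over the whole course is a legitimate quantity, and longer treatment really does produce more events. That justifies reporting it. It does not make it a good test of whether the drug raises the risk of events, because it mixes any harm with longer exposure.

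**Conclusion.** The point holds in conditional form and is a cheap improvement, not a serious flaw. The planned test of adverse-event incidence has no person-time basis, and Table 1 implies that observation closes at diabetes. If it does, and the design hazard ratio of 0.75 is true, the Jinlida arm is observed about 9% longer (6% with a 2-year cap on medication). The chance of a false signal then rises only slightly for rare events and materially for common events or the overall comparison, nearly always against Jinlida in the latter cases. The size rests on constant hazards, equal and assumed adverse-event rates, and no other dropout. The statement that the test gives false safety signals would go too far: it raises their probability, by little for most individual events, and not through this mechanism at all if adverse events are followed to a common end in both arms.

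**What to change.** 1. State whether study drug, and separately adverse-event observation, end when diabetes is diagnosed. Reconcile the Treatment, Intervention Cycles and Sample Size Calculation sections and Table 1 on treatment and follow-up duration.
2. Keep the numbers of occurrences, numbers of cases and percentages as description, and show person-years per arm beside them.
3. Base the between-group comparison on first events per 100 person-years, with a rate ratio and 95% CI from a Poisson model with log person-time as offset, or on time-to-first-event incidence at fixed months.

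The cost is a few extra columns in the safety tables; dispensing, recovery and visit dates are already collected. The Poisson version relies on a roughly constant event rate, and the fixed-month version is the alternative where that is doubtful. If observation does end at diabetes, both treat it as censoring unrelated to adverse-event risk, and the plan should say so.
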